## Abstract

**Background:**

Overconsumption of energy from food contributes to high rates of overweight and obesity in many populations. A promising set of interventions tested in pilot studies in worksite cafeterias, suggests energy intake may be reduced by increasing the proportion of healthier *–* i.e. lower energy – food options available, and decreasing portion sizes. The current study aims to assess the impact on energy purchased of *i.* increasing the proportion of lower energy options available; *ii.* combining this with reducing portion sizes, in a full trial.

**Methods:**

A stepped-wedge randomised controlled trial in 19 worksite cafeterias, where the proportion of lower energy options available in targeted food categories (including main meals, snacks, and cold drinks) will be increased; and combined with reduced portion sizes. The primary outcome is total energy (kcal) purchased from targeted food categories using a pooled estimate across all sites. Follow-up analyses will test whether the impact on energy purchased varies according to the extent of intervention implementation.

**Discussion:**

This study will provide the most reliable estimate to date of the effect sizes of two promising interventions for reducing energy purchased in worksite cafeterias.

**Trial registration:**

The study was prospectively registered on ISRCTN (date: 24.05.19; TRN: ISRCTN87225572; doi: 10.1186/ISRCTN87225572).

## Background

Unhealthy patterns of food consumption, including excess energy intake, contribute to high and rising rates of obesity worldwide (GBD [1–3]), which leads to increasing incidences of type 2 diabetes and 13 different types of cancer [4]. Providing information about obesity to the public is a popular strategy [5], but has little or no effect at changing patterns of behaviour at the scale needed [6, 7]. In part, this reflects the powerful impact of environmental cues that shape unhealthier behaviours, regardless of intentions to act differently [8, 9]. Changing these environmental cues is, therefore, key to achieving the scale of behaviour change needed to tackle obesity [10, 11].

Three Cochrane reviews highlight the potential of three sets of interventions that involve cues in the physical micro-environment: increasing the availability of healthier foods [12], reducing portion sizes [13], and adding calorie labelling [14]. These reviews also draw attention to the paucity of high-quality studies that have been conducted in real-world settings. To address this, a series of pilot studies were conducted to assess the impact on energy purchased in worksite cafeterias of these three interventions [15], a particularly important environment to target for interventions as an estimated 11–18% of an adult’s meals occur while at work [16]. The results provide preliminary evidence for the effectiveness of the availability and portion size interventions [17, 18], but not for labelling interventions [19, 20].

There is currently a small evidence base for availability interventions – only six studies met the inclusion criteria for the Cochrane review assessing impact on selection or consumption of altering the availability of food, alcohol or tobacco products [12]. Providing fewer options of a targeted food or food category led to a large reduction in their selection but with wide confidence intervals. One of the studies in the Cochrane review was the pilot study in worksite cafeterias, which resulted in a reduction of 7% in energy (kcal) purchased per day from the targeted food categories across six cafeterias, with no significant impact on revenue [18]. A similar effect was seen in a recent field study increasing the availability of vegetarian meal options (and decreasing the availability of meat ones) on selection in student cafeterias [21].

In terms of interventions targeting portion sizes, there is substantial experimental evidence that portion size reductions reduce selection and consumption of food [22, 23]. The Cochrane review that investigated size interventions included 69 studies in food, estimating that consistently reducing portion sizes could reduce energy intake by up to 16% in UK adults [13]. It also highlighted some key outstanding uncertainties, in particular the relative absence of evidence from real-world settings and over sustained time periods. One concern with the real-world application of this intervention is that customers are more likely to choose larger portions when larger options are available, thereby potentially undermining this intervention if changes are not applied to every available product. A further concern is that consumers may compensate by purchasing more products if they perceive that their portion is too small. Some evidence suggests that, contrary to a compensatory mechanism, portion size reductions may change related norms, leading consumers to purchase smaller food items in the future [24, 25], but it is unclear if this effect is generalisable; particularly to those with physically tiring jobs. A recent pilot trial in six worksite cafeterias reduced the portion size of main meals, sides, desserts, and cakes by approximately 10–15%, which led to a statistically non-significant but numerical reduction in energy purchased from intervention categories of approximately 8% [17]. However, larger field trials that recruit more sites and test interventions for longer periods of time are needed to provide more precise estimates for the effectiveness of both availability and portion size interventions.

The proposed study will provide the most reliable estimate to date of the effect sizes of two promising interventions for reducing energy purchased in 19 worksite cafeterias: increased proportion of lower energy foods available for selection, assessed on its own and in combination with reduced portion sizes. The cafeterias are located across Great Britain, serving mainly manual workers, a group with typically poorer diets, as reflected in their higher rates of obesity, type 2 diabetes and associated cancers [4]. Manual workers therefore have more to gain than non-manual workers from effective interventions. Study hypotheses: 1. fewer calories will be purchased during the availability intervention period when compared to the baseline; 2. fewer calories will be purchased during the availability + portion size intervention period when compared to the baseline and when compared to the availability intervention period.

## Methods

### Study design

A stepped-wedge design (Campbell & Walters, 2014) will be used, with each of the 19 sites randomly allocated to the time at which they implement each of the two interventions across a period of 25 weeks (see Additional file 2). This design was selected over a parallel groups cluster RCT due to insufficient resources to implement the intervention(s) at all sites simultaneously. Weeks 1 to 4 will comprise the minimum baseline period – during which data will be recorded without any intervention – followed by 21 weeks during which interventions will be introduced and maintained. From Week 5 until Week 13, two sites a week will implement the first intervention – Availability. In Week 14, the 19th site will implement this intervention. From Week 13 until Week 21, two sites a week will implement the second intervention – Size – while continuing the Availability intervention. In Week 22, the 19th site will implement this intervention. The interventions will continue until the end of Week 25 for all sites (the duration of the Size intervention in sites will therefore vary between 4 and 13 weeks).

The study was prospectively registered on ISRCTN (10.1186/ISRCTN87225572). Any significant modifications to the study will be updated on this registration.

### Interventions

#### Increased availability of healthier foods (Availability)

Availability interventions applied to products can be conceptualised into three broad categories: changing the relative availability of products, changing the absolute availability of products, or changing both [26]. The intervention in the current study comprises increasing the number of healthier food options and decreasing the number of less healthy food options to maintain the same total number of options (i.e. changing the relative availability). In the TIPPME intervention typology [10] it is classified as an Availability x Product intervention.

In the current study, healthiness is defined by energy content, with the term ‘healthier’ indicating lower energy (kcal) foods according to cut-off points varying by product type (e.g., main meal, cold drink, etc.) (see Additional file 1). Exceptions include fruit, vegetables, nuts and seeds without added sugar or salt, and 100% fruit juice, which are classed as healthier regardless of energy content. Energy content is not the only factor in determining the healthiness of a specific food item, but we have selected it because excess energy is a major contributor to population-level excess weight and obesity. It also enables an unambiguous and quantifiable scale of healthiness. The proposed implementation of this intervention is similar to that of our pilot trial [18]. A visual representation of the Availability intervention is provided in Additional file 4.

The target proportion of less healthy/healthier items varies by intervention category and is dependent on the availability of lower energy options that can be procured and introduced by the companies that provide the food and drink to the cafeterias. Where possible, the highest energy options will be selected to be removed, to maximise the effectiveness of the intervention (see Additional file 1). Items that are removed will be replaced with similar products that have a calorie content below the cut-off for the respective food category (see Additional file 1).

#### Reduced portion size (Size)

This intervention comprises reducing the portion size, by volume, of products in the targeted food categories (see Additional file 1). Within the TIPPME intervention typology [10] this is classified as a Size x Product intervention.

Within targeted food categories, changes will be requested only for products classified as less healthy using the cut-offs listed in Additional file 1. These will include – but not be limited to – all products that are served in trays (e.g. pies), countable in pieces (e.g. scampi), wet/served with a ladle (e.g. curry, rice) or sliced or portioned by the sites (e.g. cakes), as these enable reductions to be made most readily and precisely. The reductions in portion size will vary by site and specific product but will be requested to be at least a 10% reduction by volume in each targeted product. We will also request that any reduction in portion size is accompanied by an equivalent change in price.

The Availability intervention will be implemented and evaluated on its own. Following this, the Size intervention will be added to evaluate the combined effect of these two interventions. This design was selected for two reasons. First, it allows us to assess Availability in isolation, as the pilot studies indicated this was the more effective intervention, before then assessing the combined effect. Second, it ensures that the foods offered are similar across the two interventions, because implementing the Availability intervention involves altering some of the foods offered, unlike the Size intervention.

#### Fidelity checks

Researchers will carry out visits to each worksite cafeteria to monitor the baseline food offer (one visit), the implementation of the Availability intervention (two visits), and the implementation of the Size + Availability intervention (two visits). If concerns are raised about the implementation of an intervention during this visit the following occurs:
i.The researcher sends a detailed description of her/his concerns to the study manager (JR);ii.The catering manager for the site is contacted with a view to addressing the concern that working day;iii.A follow-up visit is arranged - if possible – within two working days.

These visits along with regular communications with a manager at each site are also conducted to promote site retention and engagement.

#### Blinding

Cafeteria staff will be aware of the nature of each intervention to enable the implementation of the interventions. Customers will be told via posters that a health initiative is being implemented to improve the healthiness of the food and drink on offer in the cafeteria. They will not be informed about the actual changes.

### Targeted food categories for availability and/or portion size interventions

The precise food categories and products within those that receive each of the interventions will depend on discussions with cafeteria managers and catering companies but will likely include the following:
*Main meals*: meat or vegetarian principal element of a meal*Sides*: carbohydrate rich portions (e.g.*,* chips)*Desserts:* hot desserts (e.g.*,* crumbles), dessert pots (e.g.*,* yoghurt, cheesecake, mousse, jelly, granola) and sliced cake*Bakery*: freshly made cakes, muffins, cookies, pre-packed croissants and flapjacks*Savoury snacks:* e.g.*,* crisps*Confectionery*: e.g.*,* chocolate bars, sweets*Cold drinks*: e.g.*,* cans of sugar sweetened beverages, bottles of water*Sandwiches:* pre-packaged sandwiches, baguettes, panini

Intervention categories are defined as a category of food or drink in which we had formal agreement to change the product range or product size as part of the Availability or Size interventions. Categories that we anticipate will not receive the interventions include soups, breakfasts, and items in vending machines.

### Setting

#### Participants and recruitment

We assessed eligibility of 29 cafeterias based in supermarket distribution centres. Two sites were excluded due to difficulty of access, two were excluded due to employing fewer than 350 workers, and a further six were excluded due to practical problems with the consistent mapping of the electronic till buttons (see Additional file 3).

These exclusions resulted in 19 eligible sites, all of which agreed to take part in the study. Each of these sites employ between 530 and 1453 workers and are based in England, Scotland, or Wales. All sites belong to the same UK-based supermarket chain and are managed by one of three separate catering companies.

#### Inclusion criteria

The cafeteria is based in a distribution centre that belongs to the UK-based supermarket chain that we have partnered with for this projectThe distribution centre has at least 350 employeesThe cafeteria has Electronic Point of Sale tills which can record sales data electronically

#### Exclusion criteria

Not meeting the inclusion criteriaSite is too difficult to access (requiring travel by air or sea)

#### Sample size determination

The sample size calculation was based on two pilot previous studies [17, 18]. We conservatively used the largest estimate of standard deviation (0.111) when analysis was on the log scale. A one-sided t-test at 80% power with 5% significance level and *n* = 19 cafeterias would be able to detect an effect size of 6.5% or greater reduction in energy purchased (i.e. equivalent to a reduction of − 0.067 on the log scale). We selected a one-sided test, reflecting existing evidence. This includes previous worksite studies of the same interventions to be evaluated in the current study – Availability and Size [17, 18] – in which there were reductions in 11 of 12 cafeterias using the same primary outcome as will be used in the current study – i.e. energy purchased in intervention categories. This overall direction of effect is also evident in the findings of Cochrane reviews of each of these two interventions: both interventions reduce selection of less healthy foods [12, 13].

The study duration was balanced against pragmatic considerations which results in a 25-week design with up to two sites randomised to an intervention each week.

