#### Withdrawal of participants

Further power calculations suggest that if any cafeterias drop out then *n* = 14 cafeterias would detect an effect size of 8%, *n* = 11 for 9%, and *n* = 10 for 10%.

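### The 6.5% detectable effect comes from a t-test on 19 site values, not from the stepped-wedge mixed model, so 80% power is not established for any of the three contrasts

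*Protocol article*

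**What the plan says.** Sample size determination gives one power statement. It takes its SD from two pilot studies ("We conservatively used the largest estimate of standard deviation (0.111) when analysis was on the log scale") and applies "A one-sided t-test at 80% power with 5% significance level and" 19 sites. The result is that 19 "cafeterias would be able to detect an effect size of 6.5% or greater reduction in energy purchased", equated to a reduction of "0.067 on the log scale". The section does not say what 0.111 is the SD of, whether the t-test is paired, or which comparison the 6.5% belongs to. Trial duration is justified there on pragmatic grounds only.

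Withdrawal of participants extends the claim: "Further power calculations suggest that if any cafeterias drop out then" 14, 11 and 10 sites would detect 8%, 9% and 10%.

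Elsewhere the article describes a different structure. Study design sets a 25-week stepped wedge with two successive roll-outs. Availability starts in two sites a week over Weeks 5 to 13, and then "In Week 14, the 19th site will implement this intervention". Size is added in two sites a week over Weeks 13 to 21, with the last site in Week 22. The hypotheses at the end of the Background name three contrasts: Availability versus baseline, Availability + Size versus baseline, and Availability + Size versus Availability. Data analysis / statistical plan specifies generalised linear mixed models.

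**The concern.** A t-test on one value per site assumes that each site's change is free of calendar-time effects, and it covers a single comparison. The trial staggers two interventions over 25 weeks and tests three comparisons. When time is adjusted for, a stepped wedge draws its information mainly from weeks in which sites are in different states, and here that overlap is uneven. Baseline and Availability + Size coexist in one week only. A power figure that ignores this may be too high, and it cannot be equally right for all three contrasts.

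The margin is thin. The Background reports a 7% reduction in the Availability pilot, just above the claimed 6.5%. If true power at that size is well under 80%, an inconclusive result could be given more weight against the intervention than it deserves.

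**Working it through.** **Inputs from the article.** SD 0.111 (log scale), n = 19, one-sided alpha 0.05, power 80%, effect 0.067 (Sample size determination); roll-out weeks (Study design); contrasts (Background); mixed model (Data analysis / statistical plan).

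**1. Reproducing the stated figure.** One-sample or paired t-test, 18 df, SE = 0.111/√19 = 0.0255.
- Power at 0.067 (noncentral t): 81.2%.
- Effect detectable at 80%: 0.0658, and 1 − exp(−0.0658) = 6.4%.
- Same formula at n = 14, 11 and 10: 7.5%, 8.6% and 9.0%, against the stated 8%, 9% and 10%, so those appear rounded up.
- Variants that fit less well at n = 19: two-sided paired 7.3%; one-sided two-sample 8.7%; normal approximation 6.1%.

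The stated numbers are therefore consistent with a single-contrast test on 19 site values. No step, week, correlation or mixed-model term enters.

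**2. The layout.** Sites in each state, counted from the schedule:

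| Week | Baseline | Availability | Availability + Size |
|---|---|---|---|
| 4 | 19 | 0 | 0 |
| 12 | 3 | 16 | 0 |
| 13 | 1 | 16 | 2 |
| 14 | 0 | 15 | 4 |
| 22 | 0 | 0 | 19 |

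Baseline and Availability + Size are concurrent only in Week 13 (1 site versus 2). With week effects in the model, that contrast has to be built mostly by chaining the two single steps.

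**3. Power under the stepped-wedge layout.** Generalised least squares variance for 19 sites × 25 weekly cells, with a random site intercept, fixed week effects, and terms for Availability and for added Size. Power = Φ(0.067/SE − 1.645). The article gives no weekly residual SD, autocorrelation or effect heterogeneity, so these are assumptions.

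If 0.111 is the SD of a site's change and arises wholly from independent weekly noise, the implied weekly SD follows from the schedule. The average over sites of (1/baseline weeks + 1/8 Availability weeks) is 0.2627, so the weekly SD is 0.111/√0.2627 = 0.217. Heterogeneity means a random site-specific effect for each step, independent between steps, taking the stated share of 0.111².

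| Reading of 0.111 (week effects fitted) | A vs baseline | A+S vs A | A+S vs baseline |
|---|---|---|---|
| Site change, all weekly noise | 44% | 44% | 24% |
| Site change, half heterogeneity | 55% | 55% | 32% |
| Site change, all heterogeneity | 84% | 84% | 59% |
| Weekly residual SD, independent | 89% | 89% | 58% |
| Site change, noise with AR(1) 0.9 | over 99% | over 99% | 92% |

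Standard errors in the first row are 0.045, 0.045 and 0.071. In the third row they are 0.0255, 0.0255 and 0.036. The t-test uses 0.0255.

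Detectable reduction at 80% power is 1 − exp(−(1.645 + 0.842) × SE). From the first to the third row this is 10.6% to 6.1% for each single step and 16.1% to 8.6% for A+S versus baseline.

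**4. Without week effects.** The first row becomes 85%, 86% and 85%. With half heterogeneity the figures are 84%, 85% and 69%; with all heterogeneity, 84%, 84% and 59%. Even then one figure does not serve all contrasts once site effects vary.

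**5. The combined contrast at a larger effect.** If the pilot effects of 7% (Availability) and about 8% (Size), both from the Background, multiply, the log effect is ln 0.93 + ln 0.92 = −0.156. Power for A+S versus baseline is then about 71% in the all-noise case (0.156/0.0705 − 1.645 = 0.57) and over 99% in the all-heterogeneity case.

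**The case against.** A reader might infer that the design fails to give 80% power for either intervention, that no contrast can reach 6.5%, or that 6.5% holds only when no time effect is fitted. The documents support none of these. The meaning of 0.111 is not stated, and single-step power with week effects runs from 44% to over 99% across defensible readings. It exceeds 80% if 0.111 is a weekly residual SD, if it is almost entirely effect heterogeneity, or if weekly residuals are strongly autocorrelated. Conversely, Availability + Size versus baseline can miss 80% with no time effect at all.

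Three further points stand. The low figures assume independent residuals with a weekly SD of 0.217, which the article neither gives nor supports; adjustment for daily transactions could lower it. Calendar time is not named under Covariates, so fitting it is an assumption here, though the usual one for a stepped wedge. And judging the combined contrast at 0.067 is strict, because the hypotheses expect it to exceed Availability alone and the pilot effects together suggest something larger.

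There is no arithmetic slip: 6.4% against 6.5% agrees, and the drop-out figures err on the cautious side. These points limit how much can be claimed about power. They do not show that the stated figure describes the planned analysis.

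**Conclusion.** The concern holds in this form: the 6.5% and the drop-out figures belong to a one-sample or paired t-test on site-level values, not to the stepped wedge, the mixed model or any named contrast. The pairing is inferred from the reproduction; the article does not say it. The 80% is therefore not established for the planned analysis, and one figure cannot hold for all three contrasts.

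The firmest result is relative: with week adjusted for, Availability + Size versus baseline is clearly less precise than either single step, because the two states overlap in one week. At 0.067 it stays below 80% in most cases examined, the exceptions being very strong autocorrelation or a weekly SD well under 0.111 (82% at 0.08). For the single steps, power may lie on either side of 80%.

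All of this rests on weekly cells, equal site weights, a normal approximation without small-sample correction (which would lower power slightly), and the assumed variance components.

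**What to change.** In Sample size determination, state what 0.111 is the SD of and which contrast the 6.5% refers to. Replace the single figure with the detectable effect for each of the three contrasts under the stepped-wedge mixed model with calendar time, over a stated range of residual SD, autocorrelation and effect heterogeneity. Assess the combined contrast at its own expected effect as well as at 6.5%. Redo the figures in Withdrawal of participants on the same basis.

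Keep the 19 sites and all three hypothesised contrasts. The two single steps have equal power in the calculations above, so precision gives no reason to rank one above the other.

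The cost is a short recalculation and revised wording. Some stated detectable effects may become less favourable.
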